### Blinding

According to the principle of blinding, group allocation information will be withheld from the subjects, data collection team and the statisticians. The subjects of both groups are blinded with the subjects in the control group receive placebo electroacupuncture therapy. Due to the profession of acupuncture techniques and the particularity of acupoints, the acupuncturists could not be blinded. They will be requested to perform the treatment according to the allocation and record any adverse events but will not assess the efficacy of the treatment. The data collection team is blinded. The team members will not be informed of the group allocation and will only be responsible for collecting data from the subjects. The statisticians are blinded. They are solely responsible for the statistical analysis and data interpretation. Unblinding will be taken if any serious adverse events happen, including serious complications caused by surgeries.

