### Data collection

For the SAS, FIRST, TCM rating scale of Gastrointestinal symptoms, GSRS, safety evaluation of electroacupuncture and evaluation of the resistance towards electroacupuncture, the questionnaires will be done in Case Report Form (CRF). Three scale questionnaires shall be filled by the patients themselves or under assistance of appointed data collectors according to the participant timeline (Table 2). Participants will complete the first questionnaire before the first treatment, while the second and the third questionnaire shall be collected after the treatment on the 3rd and 5th day respectively. Data collection will be done by data collection team instead of the acupuncturists to ensure neutrality of the results.

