### Data management

Data will be recorded on CRFs in paper form by the assessors. All original data will be stored in the medical record room of the Shanghai Seventh People’s Hospital for 3 years under the supervision of the Ethics Committee of Shanghai Seventh People’s Hospital affiliated to Shanghai University of Traditional Chinese Medicine.

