### Safety evaluation

During the treatment, adverse events (AE) will be monitored through patient reports and assessments by medical workers. Adverse events include intolerance to electroacupuncture, fainting from needling, needle retention, subcutaneous bruising, local infection, etc. If a patient is intolerant to electroacupuncture, the trial can be suspended, and they may withdraw from the study. In the case of fainting, needle retention, subcutaneous bruising, follow the general procedures for the cases mentioned above, and promptly document the actions taken. Bleeding upon needle removal is common in acupuncture, and it has been proven to have therapeutic effects. Mild bleeding during acupuncture is addressed by applying pressure with a dry cotton for quick haemostasis and is not considered an adverse event (AE). For infections, consultation with a dermatologist is recommended. If serious adverse events (SAE) occur that result in disability, pose a threat to life, or lead to death, the trial should be immediately halted. Emergency measures should be taken to actively rescue the patient, stabilize vital signs, and promptly report the incident to the responsible authorities.

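### The protocol contradicts itself on who records adverse events: the unblinded acupuncturists or the blinded data collection team. The part that rests on the acupuncturists' judgement is open to bias by arm.

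*Protocol article*

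**What the plan says.** Four sections of the protocol article bear on who handles safety data.

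- **Blinding** accepts that treatment is delivered unblinded: "Due to the profession of acupuncture techniques and the particularity of acupoints, the acupuncturists could not be blinded". It then has the acupuncturists "record any adverse events but will not assess the efficacy of the treatment". Of the data collection team it says: "The team members will not be informed of the group allocation and will only be responsible for collecting data from the subjects".
- **Data collection** names safety in the same list as the symptom, anxiety and sleep scales: "safety evaluation of electroacupuncture and evaluation of the resistance towards electroacupuncture, the questionnaires will be done in Case Report Form (CRF". The paragraph ends: "Data collection will be done by data collection team instead of the acupuncturists to ensure neutrality of the results". Questionnaires are completed before the first treatment and after treatment on days 3 and 5.
- **Data management** states: "Data will be recorded on CRFs in paper form by the assessors".
- **Safety evaluation** says that "adverse events (AE) will be monitored through patient reports and assessments by medical workers", and lists what counts: "Adverse events include intolerance to electroacupuncture, fainting from needling, needle retention, subcutaneous bruising, local infection, etc". Mild bleeding during acupuncture is not counted as an adverse event.

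**The concern.** The protocol sees that a treater who knows the allocation should not judge efficacy. It keeps the acupuncturists away from efficacy assessment but, in the same sentence, gives them the recording of adverse events. Their knowledge of the arm is not trivial. The electroacupuncture group is needled with manipulation until a muscle twitch and receives 0.5 to 2 mA; the placebo group has no manipulation and receives 0.1 mA. A practitioner may therefore expect more events in one arm and look or ask more closely there, or may under-record events caused by their own needling. The direction cannot be known in advance.

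At stake is the credibility of any statement about how the two arms compare on safety. There is also a practical risk: with several people recording and no stated order among them, one event can appear in two records that disagree, or in neither.

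**Working it through.** The protocol gives no adverse event rate and no safety precision figure, so there is no stated number to reproduce. The check is a comparison of role assignments.

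| Section | Who | Safety task | Knows the arm? |
|---|---|---|---|
| Blinding | Acupuncturists | Record all adverse events | Yes |
| Data collection | Data collection team, not the acupuncturists | Collect CRF data, with safety evaluation and resistance to treatment in the list | No (per Blinding) |
| Data management | Assessors | Complete the paper CRFs | Not stated here; No if they are the data collection team |
| Safety evaluation | Patients | Report events | No (per Blinding) |
| Safety evaluation | Medical workers | Assess events | Not stated |

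**Step 1: is there a conflict?** The first two rows assign overlapping work to different people. The second excludes the acupuncturists without qualification, and its list includes safety. No sentence divides the work (for example, session events to one group and later events to the other) or says which record forms the safety data.

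**Step 2: which events depend on the treater's judgement?** Fainting and a retained needle are plain to see, so knowing the arm should matter little. Intolerance, bruising worth noting, and the point at which bleeding stops being mild are matters of degree. The bleeding threshold is applied during treatment or when the needle comes out, with the acupuncturist present. This subset is the exposed part.

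**Step 3: can the size be estimated?** If the true event proportion is p in both arms and a fraction m of events goes unrecorded in one arm only, the apparent difference is p × m. The documents give neither p nor m. If recording is equally complete in both arms, m = 0 and the difference is zero. Purely as an assumption, p = 15% and m = 30% would give 0.15 × 0.30 = 4.5 percentage points, or 52 × 0.045 = 2.3, about 2 participants in an arm of 52. The sign reverses if the omissions fall in the other arm. This shows the mechanism and estimates nothing. The number of sessions at which the treater could be the recorder is 104 × 5 = 520 as planned, before dropout. That counts occasions; it does not measure bias.

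**Step 4: does it reach the primary outcome?** No. First flatus time is recorded by doctors who ask the participant, family or caregivers. The acupuncturists have no part in it.

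**The case against.** The strongest reply is that the sections can be read together: the acupuncturist notes what happens at the needling, the blinded team collects the questionnaires and safety evaluation, and patients and staff report the rest. The medical workers may simply include the acupuncturists, who are licensed hospital practitioners. The sentence excluding acupuncturists closes a paragraph about questionnaires and may not be meant to stop a treater noting a faint. Someone must record events during the session, and only the operator is sure to be there. Safety is not a listed outcome, and the Statistical analyses section names no adverse event test. An article may also leave the detail of event forms to the full protocol or CRF.

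Much of this stands. The division of labour is plausible and the fix keeps it. Session events do need the operator, and no between-arm safety test is stated. What does not stand is that the text already says this. The Blinding section gives the treaters all adverse events, not only those in the session, and the Data collection section excludes them without exception. That is a conflict between two stated rules, not an omitted detail.

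A reader might infer that the whole safety record comes from the unblinded treaters. The documents do not support that: blinded patients report events, other staff may assess them, and the CRF goes through the assessors. A reader might also infer that the acupuncturists' record governs who leaves the trial, because intolerance can lead to withdrawal. The protocol does not make their record the trigger, and it specifies analysis of all randomised participants.

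**Conclusion.** The point holds in a limited form. The sections conflict on who records adverse events, and the events that rest on the acupuncturist's judgement are open to ascertainment bias by arm. The acupuncturists are one source among several, efficacy is untouched, and the bias cannot be sized or signed from the documents.

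This rests on two readings: that the exclusion of acupuncturists in the Data collection section covers the safety items listed in the same paragraph, and that some comparison of events between arms will be reported even though no test is named. If the intention was the complementary reading set out under the objection, the remedy is still to write it down. The change is worth making because it is cheap and a blinded team already sees participants at suitable times.

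**What to change.** Reconcile the Blinding, Data collection, Data management and Safety evaluation sections so that they state one arrangement:

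1. The acupuncturist logs only events seen during the treatment session, in full detail, including site and current where relevant. Because such detail reveals the arm, the log is kept from the blinded data collection team until database lock.
2. The blinded team asks every participant in both arms the same structured adverse event questions at the existing day-3 and day-5 collections.
3. The blinded team's record is named as the main source for any between-arm comparison of adverse events. The session log is reported alongside it and labelled as unblinded data.
4. The text says who the assessors and medical workers are and whether they know the allocation.

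Keeping the log apart concerns only what the blinded team sees. It leaves the handling and prompt reporting of events, as the Safety evaluation section describes them, unchanged.

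The cost is protocol and CRF wording, a few added questions at visits that already take place, and two sources to reconcile after lock. One limit remains: the Discussion concedes that participants may realise they received placebo. The change removes the recorder's knowledge of the arm, not the participant's guess.

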### Interventions

The electroacupuncture treatment and placebo treatment are designed based on expert consensus [19]. The intervention will be conducted by appointed licensed acupuncturists of Shanghai Seventh People’s Hospital, each with a minimum of 5 years of clinical experience in acupuncture. They are required to receive standardized training prior to trial. This study followed STRICTA [20] guidelines:

#### Interventional group – electroacupuncture group (EG)

Participants in the EG will receive electroacupuncture therapy every day for 5 days consecutively, from the first day post-surgery onwards, each session lasts 20 min. Single-use acupuncture needles (diameter 0.30 mm, length 40 mm, China Suzhou Medical Appliance Company 20162200970, Hwato) will be inserted on acupoints Neiguan(PC6), Gongsun(SP4) bilaterally, 4 acupoints in total (Table 1), after the sites of insertion are disinfected. Acupuncturists shall then perform gentle manipulations on all acupoints until muscle twitch responses are sought from participants. Next, paired alligator clips of the electroacupuncture apparatus (China Suzhou Medical Appliance Company 20172200710, Hwato) are attached at bilateral acupoints (PC6 to SP4, lengthwise), with a continuous wave of 10 Hz and a current intensity of 0.5 mA to 2 mA, depending on the patient’s tolerance level. The location of acupoints is referenced from “Nomenclature and Location of Acupuncture Points” (GB/T 12346 − 2021).

**Table 1 Tab1:** Locations of Neiguan (PC 6) and Gongsun (SP 4)

Acupoints	Locations	Depth of insertion
Neiguan (PC 6)	On the palmar aspect of the forearm, 2 cun above the transverse crease of the wrist, between the tendons of m. palmaris longus and m. flexor carpi radialis.	15–30 mm, vertically
Gongsun (SP4)	On the medial aspect of the foot, in the depression distal and inferior to the base of the first metatarsal bone	15–25 mm, vertically

#### Control group – placebo group (PG)

Participants in the PG will similarly receive electroacupuncture therapy every day for 5 days consecutively, from the first day post-surgery onwards, each session lasts 20 min. However, needles are applied on non-acupoints (1 cm apart from the acupoints of EG), with no needle manipulations performed(Fig. 2). To ensure the implementation of blinding, electrodes are attached, with a continuous wave of 10 Hz, but a lower current intensity of 0.1 mA.

**Fig. 2 Fig2:**
[figure not shown]
The location of Neiguan (PC 6) and Gongsun (SP 4) for EG and the respective locations for PG. The mark “•” on the placebo group indicates the original location of both acupoints

### Outcome assessments

#### Primary outcome

First flatus time, which will be measured since the participants return to ward after surgery until the first passage of flatus. It will be recorded by doctors via inquiry of the participants themselves, the family members or the caregivers.

### Secondary outcomes

First sign of borborygmus and recovery of defecation, which will likewise be obtained through the participants themselves, the family members or the caregivers.

Laboratory tests, which blood sampling will be taken out by the nurses whereas the laboratory department will be in-charge of the handling of the blood tests and evaluation.

Self-rating anxiety scale, SAS, to measure patient’s anxiety state within the past week, with a total of 20 questions. It includes 15 positive-scored questions and 5 negative-scored questions, ranging from 1 to 4 and 4 to 1, respectively. The standard score is obtained by the sum of the raw scores, multiplied by 1.25. A higher standard score indicates a more severe level of anxiety.

Ford Insomnia Response to Stress Test, FIRST, to observe the likelihood of patients’ sleep quality being affected under different stress conditions, with a survey test consisting a total of 9 questions. Scores range from 1 to 4 based on severity, with a total score from 1 to 36. A higher score indicates that the patient’s sleep is more significantly affected by stress.

TCM rating scale of Gastrointestinal symptoms, to assess the efficacy of treatment based on the patient’s symptoms, with a scale including 32 clinically common symptoms of gastrointestinal diseases. It comes with scores of 0, 3, 5, 7 based on severity of each symptom. The total score ranges from 0 to 238. A higher score indicates a more severity of symptoms.

Gastrointestinal Symptoms Rating Scales, GSRS, to assess the patients’ gastrointestinal symptoms. This scale consists of 15 gastrointestinal symptom-related rating items, ranging from 0 to 3 based on severity, with a total score ranging from 0 to 45. A higher score indicates a more severity of gastrointestinal symptoms.

### Follow-up

The patient fills out the Quality-of-Life Questionnaire for Cancer Patients (QoL-C30) before discharge. The researcher has the patients complete the form during follow-up visits to the outpatient department at 1 month and 3 months post-surgery. If the patient doesn’t require a follow-up visit, the researcher conducts a phone call to inquire about the patient’s status.

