**Fig. 1 Fig1:**
[figure not shown]
CONSORT flow diagram of study design

After the intervention period, the participants will receive postoperative care according to the guidelines of the Gastrointestinal Surgery department until they are discharged from hospital. Participants in the CG group will be invited to receive 5 acupuncture treatments free of charge on voluntary basis as post-trial care.

Follow-ups will be done on the first month and third month after the surgery.

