### Statistical analyses

Data is analysed on the intention-to-treat (ITT) principle using all randomized participants. SPSS 25.0 is used to analyse data, with the statistical significance set at *P* < 0.05. Normally distributed continuous variables will be represented by mean and standard deviation (‾*x ± s*), and will be analysed using independent-samples *t*-test, whereas comparison of data within groups is done through paired *t*-test. Continuous variables that do not follow a normal distribution will be represented by median (quartiles), and will be analysed using the non-parametric test. Enumeration data will be analysed using the χ2 test. Categorical variables are analysed using a rank-sum test. Repeated measure ANOVA test will be used for statistical data recorded at multiple time points.

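### At 1 and 3 months the QoL-C30 is tied to clinic visits and patients without a visit get only a status call, so follow-up quality-of-life data may be selective and incomplete

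*Protocol article*

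**What the plan says.** All quotes are from the protocol article.

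- **First completion (Follow-up):** "The patient fills out the Quality-of-Life Questionnaire for Cancer Patients (QoL-C30) before discharge".
- **1 and 3 months (Follow-up):** the researcher "has the patients complete the form during follow-up visits to the outpatient department at 1 month and 3 months post-surgery".
- **Patients who need no visit (Follow-up):** for them, "the researcher conducts a phone call to inquire about the patient’s status".
- **Who is followed up (Procedure, text below Fig. 1):** "Follow-ups will be done on the first month and third month after the surgery". This is not limited to patients who attend clinic.
- **Analysis set (Statistical analyses):** "Data is analysed on the intention-to-treat (ITT) principle using all randomized participants".

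No visible section gives a phone, postal or proxy route for the QoL-C30. The Data collection section, which describes how the other questionnaires are gathered, does not mention it. The assessment schedule (Table 2) is not shown.

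**The concern.** The form is attached to the visit. For the phone call the text changes its object from the form to the patient's status. Need for a visit is settled after randomisation. If patients who need no visit tend to be the better recovered ones, their scores are the ones not collected. If electroacupuncture helps recovery, the proportion collected could also differ between the arms.

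The QoL-C30 is the only outcome instrument named for the period after discharge. A comparison restricted to patients who attend would be less precise, could be biased, and would not be an analysis of all randomised participants. The matter belongs in the protocol because it concerns what is collected: a score not obtained at 1 or 3 months cannot be collected afterwards.

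**Working it through.** **1. The passages side by side.** Follow-up at both times is announced for participants generally, and analysis is to include everyone randomised. The only stated place for completing the form is the outpatient visit, and the alternative contact is described without the form. Taken literally, these statements do not fit together once any patient has no visit. Repeated measures ANOVA, named for data at several time points, in its usual form also drops a patient with any time point missing.

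**2. The plan's own figure.** The Sample size section gives 52 per group with 15% dropout, 80% power and two-sided α = 0.05. The dropout step is consistent with 44 evaluable per arm: 44 / (1 − 0.15) = 51.8, rounded up to 52. (45 × 1.15 = 51.75 also gives 52.) The effect size and SD are not stated, so the full calculation cannot be reproduced. It concerns first flatus time only. I use 44 per arm as the best case for the QoL-C30.

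**3. Precision.** The normal approximation for the standardised difference detectable with 80% power is d = (1.960 + 0.842) × √(2/n). The t-test value is slightly larger.

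| Forms per arm | Share of 44 | d, approximation | d, t-test |
|---|---|---|---|
| 44 | 100% | 0.60 | 0.60 |
| 40 | about 90% | 0.63 | 0.63 |
| 22 | 50% | 0.84 | 0.86 |

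With an assumed SD of 20 points, 0.60 is 12 points and 0.86 is about 17 points. The trial is not sized for the QoL-C30, so even complete collection would not give 80% power for a difference of 5 to 8 points.

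**4. Selection.** Every input here is an assumption, because the documents give neither the share of visits nor what decides them.

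- Quality of life y is in SD units (SD 20 points, higher is better). The control mean is 0 and the treated mean is 5/20 = 0.25 or 8/20 = 0.40.
- logit P(visit) = a − b·y, with b = −ln(OR) and OR = 0.5 or 0.33 per SD. So b = 0.69 or 1.11.
- a is set so that 50% or 90% of patients visit overall.
- The observed mean in an arm is the mean of y weighted by P(visit).

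| Visiting | OR per SD | Observed for true 5 | Observed for true 8 | Shrinkage |
|---|---|---|---|---|
| 90% | 0.5 | 4.8 | 7.7 | about 4% |
| 90% | 0.33 | 4.6 | 7.4 | about 8% |
| 50% | 0.5 | 4.5 | 7.2 | about 10% |
| 50% | 0.33 | 4.0 | 6.4 | about 20% |

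The observed arm means are about 1.2 to 2.3 points too low at 90% visiting and 5.9 to 9.7 points too low at 50%.

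**The case against.** The strongest reply is that the call replaces the visit, in a paragraph whose only instrument is the QoL-C30. Asking about the patient's status may simply mean putting the questions by phone. Follow-up is announced for participants generally, and Table 2 or a call script in the full protocol may settle it. This stands as a possible intention. On that reading no forms are lost, but the wording should say so, and the mode (self-completed or by interview) would still depend on need for a visit.

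Three stronger readings are tempting, and the documents do not support them:

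- **A reader might infer that data certainly go missing according to health.** The text does not say what makes a visit necessary. In patients with stage I–III tumours after surgery it could be routine review, further treatment or care elsewhere. The link with recovery is plausible, not stated.
- **A reader might infer that no analysis could help.** The pre-discharge QoL-C30 and the in-hospital scales could reduce the bias, though only under assumptions that cannot be tested.
- **A reader might infer that a pre-treatment QoL-C30 has been omitted.** The schedule is not visible, and the Data collection section does not mention this form at any time point, so its silence about baseline shows little. A randomised comparison does not need a baseline score to be valid.

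It is also fair to say that the stakes are limited. The QoL-C30 is not listed as a primary or secondary outcome.

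**Conclusion.** The concern holds in a limited form. As written, the rule makes collection of the 1- and 3-month QoL-C30 depend on a post-randomisation condition and does not fit an analysis of all randomised participants. If need for a visit falls as quality of life rises, the observed scores are too low and a true benefit is understated.

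The size is unknown. It is modest if nearly all patients visit (shrinkage 4% to 8%, detectable d 0.63) and material if only half do (10% to 20%, detectable d 0.86). Both rest on the assumed SD, true difference and selection strength given above. The large-effect case should not be taken as the expected one, since nothing in the documents points to 50% visiting.

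First flatus time, the sample size and the listed secondary outcomes are untouched. The wording should be corrected, but the point does not threaten the trial's main conclusion.

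**What to change.** State in the Follow-up section that every randomised participant completes the full QoL-C30 at 1 and 3 months: at the clinic visit if there is one, otherwise by phone within the same time windows. Record the mode of completion for each form. If the call was always meant to carry the questionnaire, the same sentence settles the ambiguity. This concerns data collection only and leaves the clinical decision about who needs a visit alone.

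The cost is a change of wording and a longer script for calls already planned. The small downside is a mixture of completion modes, which recording the mode makes visible. The change should be made before follow-up data are lost.
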